# Q-HAM: a multicenter upfront randomized phase II trial of quizartinib and high-dose Ara-C plus mitoxantrone in relapsed/refractory AML with FLT3-ITD

**DOI:** 10.1186/s13063-023-07421-x

**Published:** 2023-09-15

**Keywords:** Quizartinib, Relapse, Refractory, Acute myeloid leukemia, Measurable residual disease, Matched threshold crossing approach

## Abstract

**Background:**

About 50% of older patients with acute myeloid leukemia (AML) fail to attain complete remission (CR) following cytarabine plus anthracycline-based induction therapy. Salvage chemotherapy regimens are based on high-dose cytarabine (HiDAC), which is frequently combined with mitoxantrone (HAM regimen). However, CR rates remain low, with less than one-third of the patients achieving a CR. *FLT3*-ITD has consistently been identified as an unfavorable molecular marker in both relapsed and refractory (r/r)-AML. One-quarter of patients who received midostaurin are refractory to induction therapy and relapse rate at 2 years exceeds 40%. The oral second-generation bis-aryl urea tyrosine kinase inhibitor quizartinib is a very selective *FLT3* inhibitor, has a high capacity for sustained *FLT3* inhibition, and has an acceptable toxicity profile.

**Methods:**

In this multicenter, upfront randomized phase II trial, all patients receive quizartinib combined with HAM (cytarabine 3g/m^2^ bidaily day one to day three, mitoxantrone 10mg/m^2^ days two and three) during salvage therapy. Efficacy is assessed by comparison to historical controls based on the matched threshold crossing approach with achievement of CR, complete remission with incomplete hematologic recovery (CRi), or complete remission with partial recovery of peripheral blood counts (CRh) as primary endpoint. During consolidation therapy (chemotherapy and allogeneic hematopoietic cell transplantation), patients receive either prophylactic quizartinib therapy or measurable residual disease (MRD)-triggered preemptive continuation therapy with quizartinib according to up-front randomization.

The matched threshold crossing approach is a novel study-design to enhance the classic single-arm trial design by including matched historical controls from previous clinical studies. It overcomes common disadvantages of single-armed and small randomized studies, since the expected outcome of the observed study population can be adjusted based on the matched controls with a comparable distribution of known prognostic and predictive factors. Furthermore, balanced treatment groups lead to stable statistical models. However, one of the limitations of our study is the inability to adjust for unobserved or unknown confounders.

Addressing the primary endpoint, CR/CRi/CRh after salvage therapy, the maximal sample size of 80 patients is assessed generating a desirable power of the used adaptive design, assuming a logistic regression is performed at a one-sided significance level *α*=0.05, the aspired power is 0.8, and the number of matching partners per intervention patient is at least 1. After enrolling 20 patients, the trial sample size will be recalculated in an interim analysis based on a conditional power argument.

**Conclusion:**

Currently, there is no commonly accepted standard for salvage chemotherapy treatment. The objective of the salvage therapy is to reduce leukemic burden, achieve the best possible remission, and perform a hemopoietic stem-cell transplantation. Thus, in patients with *FLT3*-ITD mutation, the comparison of quizartinib with intensive salvage therapy versus chemotherapy alone appears as a logical consequence in terms of efficacy and safety.

**Ethics and dissemination:**

Ethical approval and approvals from the local and federal competent authorities were granted. Trial results will be reported via peer-reviewed journals and presented at conferences and scientific meetings.

**Trial registration:**

ClinicalTrials.gov NCT03989713; EudraCT Number: 2018-002675-17.

**Supplementary Information:**

The online version contains supplementary material available at 10.1186/s13063-023-07421-x.

## Background

Intensive chemotherapy consisting of induction and consolidation therapy is given with curative intent in most of the patients with acute myeloid leukemia (AML) except for old and frail patients [1–3]. Despite intensive therapy, the long-term outcome of AML patients remains poor, with less than 30% of patients achieving long-lasting remission or even cure [1, 2]. This poor outcome is mainly due to refractoriness to induction chemotherapy and relapse during and after completion of intensive induction and consolidation therapy. About 20–30% of AML patients under the age of 60 years and about 50% of older patients fail to attain complete remission (CR) following cytarabine plus anthracycline-based standard induction therapy [4–6]. Furthermore, patients having achieved CR are at a high risk of relapse, particularly within the first 2 years after completion of chemotherapy [7].

Allogeneic hematopoietic cell transplantation (allo-HCT) is currently the only treatment strategy to offer the prospect of a cure in relapsed/refractory (r/r-) AML. The outcome of allo-HCT is heavily influenced by the remission state before allo-HCT [8–12], and according to recent publications, measurable residual disease (MRD) positivity in both peripheral blood and bone marrow (BM) was consistently revealed to be a poor prognosis factor regarding relapse rate [8, 9]. Salvage chemotherapy regimens are administered in r/r-AML to induce CR before allo-HCT. Typically, these salvage regimens are based on high-dose cytarabine (HiDAC), which is frequently combined with either mitoxantrone (HAM regimen) or fludarabine plus idarubicin (idaFLA regimen) [10]. However, there is still no commonly accepted standard salvage regime, and overall CR rates are low [10].

Internal tandem duplications of the FMS-related tyrosine kinase 3 (*FLT3*-ITD) have consistently been identified as an unfavorable molecular marker in both relapsed and refractory AML [7, 10]. Furthermore, patients with refractory disease exhibiting a *FLT3*-ITD showed, despite an allo-HCT, a hazard ratio (HR) of 1.5 (95% CI 1.2–1.7) higher probability of death [6].

Midostaurin is currently the only tyrosine kinase inhibitor (TKI) that has demonstrated superior results compared to standard intensive therapy in younger *FLT3*-mutated newly diagnosed AML patients for all survival endpoints, including overall survival [11]. Midostaurin is now approved for the treatment of AML in newly diagnosed patients with an activating *FLT3*-mutation in combination with intensive induction, consolidation including allo-HCT, and maintenance therapy in the EU. Furthermore, based on a phase II follow-up study of the RATIFY trial, the approval was extended to older patients aged between 60 and 70 years [12]. However still, roughly one-quarter of patients in the midostaurin arm of the study were refractory to induction therapy and relapse rate at 2 years exceeded 40% [11]. Thus, new treatment options are urgently needed, particularly for r/r-AML with *FLT3*-ITD.

The oral second-generation bis-aryl urea inhibitor quizartinib is a very selective* FLT3* inhibitor, has a high capacity for sustained *FLT3* inhibition, and an acceptable toxicity profile [13]. In a phase II study (*n*=333), quizartinib demonstrated particular efficacy in patients with *FLT3*-ITD mutations (*n*=248), who were relapsed or refractory to 2nd-line, salvage chemotherapy, or relapsed after allo-HCT [14]. The response to single-agent quizartinib in *FLT3*-ITD-positive patients was overall 50.4% (125/248), 56% in patients with r/r-AML within the first-line therapy first year, and 46% after allo-HCT. A subsequent phase II study recruited 76 patients with *FLT3*-ITD mutations with r/r-AML after either one second-line therapy or allo-HCT. Patients were randomized to single-agent quizartinib 30mg/day (Group A) or 60mg/day (Group B) given as single agent orally during 28-day continuous treatment cycles, until relapse, intolerance, or proceeding to allo-HCT. The response rate was 61% in Group A and 71% in Group B. In addition, 32% of patients in Group A and 42% in Group B could be successfully bridged to allo-HCT [15]. Recently, first results of the randomized study in relapsed (with a duration of first CR of 6 months or less)/refractory AML have been reported comparing single-agent quizartinib (*n*=245) to investigator’s choice (*n*=122) [16]. In this setting, single-agent quizartinib improved OS significantly (HR 0.76, 95% CI 0.58–0.98; stratified log-rank test, 1-sided *P*=0.0177). Median OS was 27 weeks (95% CI 23.1–31.3) and 20.4 weeks (95% CI 17.3–23.7) for patients treated with quizartinib and investigator’s choice, respectively. At 1 year, the estimated OS probability was 27% for the quizartinib and 20% for investigator’s choice. Although quizartinib was superior compared to investigator’s choice, results may improve when quizartinib is combined with intensive chemotherapy.

Feasibility of combination therapy with quizartinib and chemotherapy has been shown in several phase II trials [17, 18] inducing a double-blinded, randomized phase III study of quizartinib with induction and consolidation chemotherapy and as maintenance in patients with newly diagnosed *FLT3*-ITD AML (ClincalTrials.gov identifier: NCT02668653) [19].

Regarding dosage and schedule, in the first-in-human phase I study, CP0001, quizartinib was administered with intermittent dosing (14 days on drug followed by 14 days rest) from 12 to 450mg and continuous dosing at 200mg and 300mg for 28 days in 76 patients with r/r-AML, regardless of *FLT3*-ITD mutation status [13]. Plasma taken from subjects and assayed in an in vitro plasma inhibitory assay (PIA) showed rapid and durable inhibition of *FLT3* phosphorylation as early as 2 h after the first dose. The overall response rate was 53% in *FLT3*-ITD mutated and 14% in *FLT3*-ITD unmutated patients [13].

The response rate observed in Study CP0001 was confirmed in the phase II study, AC220-002, of single-agent quizartinib in r/r AML. In this phase II study, a total of 333 patients were enrolled in 2 cohorts; Cohort 1 included patients 60 years or older who were relapsed or refractory to the first line of therapy, and Cohort 2 included patients 18 years or older who were relapsed or refractory to salvage therapy or relapsed after allo-HCT. In Cohort 1, the composite complete remission (CRc) rate was 57% in *FLT3*-ITD mutated patients with a median survival of 25.3 weeks [20, 21]. Cohort 2 showed a CRc rate of 46% in *FLT3*-ITD mutated patients with a median survival of 24.0 weeks [20]. Notably, 35% of Cohort 2 *FLT3-*ITD mutated patients were bridged to allo-HCT [22].

The maximum tolerated dose (MTD) determined in the phase I study, CP0001, was 200mg continuous daily dosing [13]. However, in the phase II study AC220-002, 35% of patients experienced grade 3 QT prolongation at the 200mg dose, and therefore the dose was reduced. A single case of grade 4 QT prolongation, Torsades de Pointes, was reported in the AC220-002 Study in a patient with pneumonia, atrial fibrillation, taking concomitant medications known to cause QT prolongation [23]. No deaths related to QT prolongation have been reported [20].

The phase IIb 2689-CL-2004 Study was subsequently conducted. A total of 76 patients with *FLT3-*ITD-mutated AML were randomized to 60mg or 30mg quizartinib daily to examine the efficacy and toxicity at these lower doses. Both males and females were randomized to each dose. The study showed that the CRc rate was similar for both doses and to the rate observed in the earlier AC220-002 Study [24].

Common adverse events (AEs) observed in the phase I and II studies included gastrointestinal disorders (nausea, diarrhea, and vomiting), hematologic disorders (anemia, neutropenia, and thrombocytopenia), febrile neutropenia, fatigue, and QT prolongation.

Although hematologic toxicity is associated with the underlying disease, safety reports from Study AC220-002 in AML indicate delayed recovery or continued suppression of absolute neutrophil counts (ANC) and platelets as a consequence of continued treatment with quizartinib [20].

Based on phase I and phase II studies’ results, it appears reasonable and clinically feasible to combine salvage therapy with quizartinib in patients with r/r- *FLT3*-ITD mutated AML. This manuscript describes the rationale, design, and dosing details of the Q-HAM study (clinicaltrials.gov identifier NCT03989713; EudraCT No 2018-002675-17), a phase II study comparing quizartinib adjunct to salvage therapy to historical controls based on the matched threshold crossing approach.

The primary objectives of the study are (i) to assess the clinical efficacy of quizartinib in combination with high-dose cytarabine and mitoxantrone and (ii) to assess the clinical efficacy of MRD-triggered and preemptive quizartinib continuation therapy in patients with r/r- *FLT3*-ITD mutated AML.

**Fig. 1 Fig1:**
[figure not shown]
Overall treatment schedule Q-HAM-Study. Abbreviations: MRD, minimal residual disease; CR, complete remission; CRi, complete remission with incomplete hematologic recovery; CRh, complete remission with partial recovery of peripheral blood counts; Q-HAM, quizartinib, high dose cytarabine and mitoxantrone; EOT, end of treatment; EOS, end of study. Please refer to Additional file 1 for a detailed SPIRIT figure

### Study setting and randomization

In Germany, patients with r/r-AML are usually referred to academic hospitals. Patients under treatment in the participating centers will be asked to participate in the study. Recruitment will take place in up to 20 academic centers registered in the Study Alliance Leukemia (SAL) group (http://www.sal-aml.org/). During the study conduct, participating centers (see Additional file 2) are contacted by study monitors and the medical coordinator monthly to promote patient recruitment. Furthermore, after protocol amendments or upon relevant updates during the study, a newsletter will be sent to all participating centers. Conferences with the participating centers of the SAL network are held regularly to share information regarding therapy responses and complications seen within the study. Expecting at least 5 potentially eligible patients per year and center, approximately 2 years are required to recruit the anticipated number of patients, when accounting for a consecutive study center initiation and non-participation.

Patients have to provide written informed consent and must meet all inclusion criteria before any protocol-specific procedures are performed.

Each patient must be registered in the electronic case report form (eCRF). During registration, a unique patient ID (PAT-ID) is assigned. Following registration, all eligible patients are upfront 1:1 randomized. The randomization step is triggered by the study sites using a centralized web-based tool (randomizer.at) configured by the responsible data management team. Randomization is performed stratified according to previous treatment with midostaurin. Forty patients are allocated to each arm. Twenty or more centers are selected to recruit the intended number of patients. The treatment arms are (a) the MRD-triggered arm and (b) the prophylactic arm.

### Post-randomization events

In case a patient prematurely withdraws from the trial or is lost to follow-up before measurement of the primary endpoint, this patient’s response is set to missing. In case a patient dies due to any cause before CR/ or CR with incomplete hematological recovery (CRi) or complete remission with partial recovery of peripheral blood counts (CRh) measurement, the primary endpoint will be set to “no Composite Remission”.

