### Withdrawal of patients

A patient must be withdrawn from the trial (i) at any time at the patient’s own request, (ii) after salvage therapy if the patient fails to obtain CR/Cri/CRh, (iii) at any time if unacceptable toxicity necessitating cessation of treatment is observed, (iv) at any time if there are changes in the medical status of the patient that compromise the patient’s safety or if the investigator considers that the withdrawal is in the patient’s best interest, (v) in case of pregnancy, (vi) at any time a patient’s protocol compliance turns out insufficient, and (vii) if patient is lost to follow-up.

If any of the aforementioned criteria are met, and patients agree to follow-up, previous unresolved AEs will continuously be followed. If cases iii and iv are met we will continue with the follow-up of the patient until the end of the study. However, if the patient withdraws from the trial and also from consent for disclosure of future information (e.g., follow-up visits), further data collection is prohibited.

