The sample size required for a fixed design, assuming CR/CRi/CRh rates of 0.55 for the enrolled patients and 0.30 for the historical controls, would be a minimum of 60 assuming a logistic regression is performed at one-sided significance level *α*=0.05, the aspired power is 0.8, and number of matching partners per intervention patient is at least 1. Using this sample size as a starting point for several simulation studies, it was assessed that the maximal enrolment of 80 patients generated a desirable power of the used adaptive design for most scenarios. The trial sample size is recalculated based on a conditional power argument in an interim analysis after enrolling 20 patients and will hence range between 20 and 80. The assumed CR/CRi/CRh rate of 0.3 for historical controls was estimated based on two large IPD meta-analyses datasets of r/r-AML patients (“historical control”) [6, 7], while the assumed CR/Cri/CRh rate of 0.55 for the patients treated quizartinib was determined to reflect a treatment effect that can be considered as clinically relevant. The sample size for the fixed design was calculated using the software PASS v16, while the simulations we used to evaluate the adaptive design were done using R v3 (http://r-project.org). Randomized patients who do not receive the IMP quizartinib will be replaced. All patients receiving at least one dose of the IMP quizartinib must not be replaced. Due to the underlying disease, loss to follow-up is expected to be negligible.

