For the analysis of the primary endpoint, a logistic regression model will be applied to assess the odds ratio of CR/CRi/CRh rate after salvage therapy for patients receiving Q-HAM versus matched controls not receiving Q-HAM. The null hypothesis H0: OR≤1 is tested against its alternative H1: OR>1 at a one-sided significance level of *α*=0.05. The logistic regression analysis will be adjusted for age, high-risk cytogenetics (yes/no), and CR1 duration <18 months (yes/no/not applicable due to refractory disease). Due to the adaptive nature of the trial, two separate logistic models will be fitted for the two trial stages and be combined using the inverse normal function approach. Determination of *p*-values, point, and interval estimates will take the adaptive nature of the trial into account. Concerning the secondary endpoints: EFS, OS, and RFS endpoints will be analyzed using a Cox regression model and Kaplan-Meier plots, CIR, and CID will be analyzed according to Gray 1988 [33] and via cumulative incidence plots, and quality of life will be analyzed descriptively according to the corresponding guidelines and EORTC recommendations. Safety endpoints will be analyzed descriptively. Analyses of the primary and secondary endpoints will be based on the full analysis population (all randomized patients with treatment groups assigned in accordance with the randomization, regardless of the treatment actually received (intention to treat (ITT)). For patients with incomplete follow-up, time to last follow-up date will be used as the censoring time in the analysis of time-to-event data. Otherwise, no imputation of missing data will be conducted. For the biometricians, patient treatment shall remain blinded from the time of randomization until the final database lock. The interim analysis and sample size recalculation will be conducted by an independent biometrician who is not involved in the conduct of the trial. Statistical analysis will be performed using SAS v9.4 or higher [34].

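### Living patients who leave before the remission assessment drop out of the primary analysis; if they respond less often than assessed patients, the Q-HAM response rate and odds ratio are biased upwards

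*Protocol article*

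**What the plan says.** All places are in the protocol article.

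- **Post-randomization events.** The rule for early leavers begins "In case a patient prematurely withdraws from the trial or is lost to follow-up before measurement of the primary endpoint"; their "response is set to missing". Death is treated differently. The sentence beginning "In case a patient dies due to any cause before CR" makes death before the remission measurement a failure.
- **Withdrawal of patients.** Withdrawal from the trial is mandatory for, among other reasons, toxicity (reason iii, "at any time if unacceptable toxicity necessitating cessation of treatment is observed"), a compromising change in medical status or the investigator's judgement (iv), and the case where a patient's "protocol compliance turns out insufficient" (vi). Each can occur at any time. Failure to reach remission after salvage (ii) also leads to withdrawal, but only after the outcome is known. For iii and iv the section promises follow-up to the end of the study; it gives no such promise for vi.
- **Sample size calculation and statistics.** Primary and secondary endpoints are analysed in all randomized patients, by assigned arm, "regardless of the treatment actually received". Censoring is described for time-to-event data; after that, "Otherwise, no imputation of missing data will be conducted". The section expects loss to follow-up to be negligible and is silent on withdrawal. It also states: "Randomized patients who do not receive the IMP quizartinib will be replaced".
- **Salvage therapy.** Remission is assessed around day 28, with a second control possible until day 42.

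**The concern.** A logistic model cannot use a patient without an outcome. Read together, the missing-outcome rule and the bar on imputation turn the primary analysis into a complete-case analysis of patients who were assessed or died. The excluded patients are alive, withdrawn or lost, and unassessed by about day 28 to 42.

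Toxicity and deterioration are plausibly linked to not reaching remission. The plan accepts that logic for deaths and applies the opposite rule to a patient withdrawn for severe toxicity who survives.

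Randomization gives no protection. It concerns only the continuation strategy; every patient receives Q-HAM during salvage, and the primary comparison is with matched historical controls. Selective loss on the Q-HAM side therefore goes straight into the estimated odds ratio, the interim futility check and the final test.

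**Working it through.** **Inputs from the statistics section.** Response 0.55 with Q-HAM and 0.30 in controls, one-sided alpha 0.05, power 0.8, at least one matched control per patient, fixed-design minimum 60, maximum 80, interim after 20 patients with an odds-ratio threshold of 1.3. **Assumed, because the documents give no figure:** withdrawn fraction w of 2% to 20%.

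**The plan's own figure.** Two proportions, 0.55 vs 0.30, one-sided 0.05, power 0.8, 1:1, give 48 Q-HAM patients (55 with continuity correction). Two-sided 0.05 gives 61. A one-sided logistic formula with an assumed covariate R-squared of 0.20 gives 59.1, hence 60. So 60 is reached under a common variant, and nothing below depends on which was used.

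**Direction of bias.** Let a be the response rate in assessed patients (deaths included as failures) and u the rate in withdrawn, unassessed patients. The rate in all patients is (1 − w)a + wu. Complete-case analysis reports a, so the bias is w(a − u). It is positive if u < a and zero if u = a.

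**Size in the extreme case u = 0.** Reported rate = all-patient rate / (1 − w). Odds ratios are against 0.30, that is odds of 0.30/0.70 = 0.4286.

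| w | true 0.55: reported rate, OR (true OR 2.85) | true 0.30: reported rate, OR (true OR 1) |
|---|---|---|
| 2% | 0.561, 2.98 | 0.306, 1.03 |
| 5% | 33/57 = 0.579, 3.21 | 0.316, 1.08 |
| 10% | 33/54 = 0.611, 3.67 | 0.333, 1.17 |
| 20% | 33/48 = 0.688, 5.13 | 0.375, 1.40 |

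**A milder case.** With true rate 0.30, w = 10% and u = 0.15: a = (0.30 − 0.10 × 0.15)/0.90 = 0.317, and OR = (0.317/0.683)/0.4286 = 1.08. That is about half the excess of the extreme case.

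**Rejection probability with no true effect.** Pooled two-proportion z test, fixed design, complete 1:1 controls, u = 0:

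P = Φ[(a − 0.30 − 1.645·SE0)/SE1]

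SE0 uses the pooled rate and SE1 the separate rates. For n = 60 and w = 10%: 54 assessed at 0.333 and 60 controls at 0.30; pooled rate 36/114 = 0.316; SE0 = √[0.316 × 0.684 × (1/54 + 1/60)] = 0.0872; SE1 = √(0.2222/54 + 0.21/60) = 0.0873; argument (0.0333 − 0.1434)/0.0873 = −1.26; P = 0.104.

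| w | n = 60 | n = 80 |
|---|---|---|
| 0 | 0.050 | 0.050 |
| 2% | 0.058 | 0.059 |
| 5% | 0.072 | 0.076 |
| 10% | 0.104 | 0.115 |
| 20% | 0.206 | 0.244 |

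**Interim illustration (crude OR against 0.30).** Seven responders and one withdrawal among 20: complete-case 7/19 gives (7/12)/0.4286 = 1.36, above 1.3. Counting the withdrawal as failure, 7/20 gives (7/13)/0.4286 = 1.26, below it. The actual rule is covariate-adjusted and non-binding, so this shows only how little is needed to cross the threshold.

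**The case against.** - **Follow-up after withdrawal.** The patients of most concern (reasons iii and iv) are followed to the end of the study, and the missing rule applies only before the endpoint is measured. A followed patient whose marrow is examined may well have a measured endpoint. This stands as a limit on the claim: a reader might infer that every toxicity withdrawal leaves the denominator, and the text does not establish that. Nor does it say that an assessment after withdrawal is used, and withdrawal for non-compliance has no follow-up promise.
- **Main failures already counted.** Deaths are failures, and refractory patients leave only after assessment. The exposed group is confined to about six weeks. This stands.
- **Error inflation is conditional.** It needs withdrawn patients to respond less often. The tables take the extreme case, and at 2% the excess is trivial. This stands.
- **Fixed design.** The planned test has two stages. Simulating an unadjusted inverse-normal test with 1:1 controls and assumed stage weights, under the same extreme assumption, gives about 0.08 to 0.10 at 10% withdrawn if the futility stop is always followed, and about 0.09 to 0.11 if it is not credited. At 2% the result stays near 0.05. The fixed-design figures are therefore a fair, slightly high guide.
- **Intention to treat.** A reader might infer a flat contradiction. The all-randomized statement says who belongs to the set and in which arm; handling of missing outcomes within the set is a separate matter. What stands is that the declared set and the patients actually modelled differ. Similarly, replacement of never-dosed patients is a recruitment rule. It fits poorly with an all-randomized set, but it does not say that those patients are removed from analysis.

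**Conclusion.** The point holds in conditional form. Followed as written, the primary model excludes living patients without a remission assessment and counts only deaths as failures among those not assessed. The bias is upwards if the excluded patients respond less often, which is plausible for toxicity or deterioration but not shown by the documents.

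Under the extreme assumption, complete 1:1 controls and a fixed design with 60 patients, the nominal 0.05 becomes about 0.058 at 2% withdrawn, 0.07 at 5% and 0.10 at 10%. A planned rate of 0.55 would be reported as 0.58 at 5% or 0.61 at 10%. These are upper figures for each withdrawal rate. They shrink if follow-up supplies assessments and vanish if withdrawal is unrelated to response. An unconditional statement that the error rate is inflated is not supported.

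The Trial status section reports early closure with 11 patients, so the planned test is largely moot. The response rate is still reportable and sensitive to the rule: with, for example, four responders, one exclusion moves 4/11 = 36% to 4/10 = 40%.

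**What to change.** 1. Replace the missing-outcome rule. A remission assessment obtained within the salvage assessment window is used even if the patient has withdrawn, including under the follow-up for reasons iii and iv. Any patient in the primary set without documented CR, CRi or CRh by the end of that window counts as a non-responder, as deaths already do. Use the same rule at the interim.
2. Apply the same rule to matched controls as far as the individual-patient datasets record unassessed patients, and state what was done where they do not.
3. Keep the complete-case analysis as a sensitivity analysis.
4. State whether replaced, never-dosed patients stay in the primary set, so that the replacement rule and the all-randomized definition agree.

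**Cost.** A few sentences, plus a check of how the control datasets code missing response. The reported rate will be somewhat lower, and the rule is conservative if withdrawal is unrelated to response. For example, with 10% unassessed and a rate of 0.55 in all patients, the counted rate is 0.55 × 0.90 = 0.495, and the odds ratio against 0.30 is (0.495/0.505)/0.4286 = 2.29 instead of 2.85. At 2% the counted rate is 0.539. The complete-case sensitivity analysis shows how much of any difference is due to this convention.
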